### 1.6 Data Safety Monitoring Committee

No Data Safety Monitoring Committee will be constituted for this study.

### **1.7.3 Supervision regarding clinical implementation of the study in the ER**

In addition, integration of the present project with current clinical practice and patients flow in the ER will be carefully cared for throughout the whole project. The study PI will closely work together with Co-Is [name], head physician at the ER, [name], head physician at the ATC, [name], associate physician at the ATC, [name] (see above) and the study clinicians to implement the study process and practices in the ER without interfering with the quality of the clinical practice, and to guarantee the ethical principle of treatment equity. Clinical supervision on these aspects will be ongoing throughout the project for study clinicians. Meeting of the clinical team, PI and Co-Is will be organized on a regular basis.

#### **1.7.4.2 Interventionists**

Two or three interventionists will be hired over the study. They will conduct both types of interventions. They will also conduct patients' recruitment and inclusion, baseline assessment, and collect post-session patient's questionnaires.

#### 1.7.4.3 Research assistants

Four research assistants will be hired over the study. Research assistants will be in charge of the follow-up assessments.

#### 1.7.4.4 Psycholinguistic coders

Five coders will be hired over the study. Their tasks will encompass audio-recorded intervention sessions coding.

## 2. ETHICAL AND REGULATORY ASPECTS

### 2.1 Study registration

The current study will be registered in the ClinicalTrials.gov registry and in the supplementary federal database (Swiss National Clinical Trials Portal (SNCTP), through BASEC application.

**Registered in the ISRCTN, # 13832949, <https://doi.org/10.1186/ISRCTN13832949>**

**(Information added 30.11.2016, before inclusion of participants in the RCT)**

### 2.2 Categorization of study

The current clinical trial comes under **Other clinical trial, category A** because it is neither a trial of therapeutic products or transplants products, nor a trial of transplantation. Next, the health-related intervention investigated (i.e., a brief alcohol-related motivational interviewing) entails only minimal and temporary risks and burdens on participants' health (i.e., well-being). Finally, the health-related intervention investigated is recognized as standard in guidelines prepared in accordance with internationally accepted quality criteria.

### 2.3 Competent Ethics Committee (CEC)

The responsible investigator ensures that approval from an appropriately constituted Competent Ethics Committee (CEC) is sought for the clinical study.

No significant change will be made to the protocol without CEC approval, except where necessary to eliminate apparent immediate hazards to study participants. In case of a significant change, the principal investigator will submit to the CEC any application documents specified in Annex 3 of ClinO that are affected by the change, while providing information on the reasons for the change. Examples of significant changes in the current study may encompass changes affecting participants' rights and obligations, changes to the protocol (e.g., changes to eligibility criteria, method of investigation, endpoints, form of statistical analysis), conducting the clinical trial at an additional site, or a change of sponsor, coordinating investigator or investigator responsible. Other minor changes will be notified to the CEC in the annual safety report.

In case of premature study end or interruption of the study, it would be reported within 15 days to the CEC. Next, the regular end of the study will be reported within 90 days and the final study report will be submitted within one year after the study end.

### 2.4 Competent Authorities (CA)

Not applicable (category A).

### 2.5 Ethical Conduct of the Study

The study will be carried out in accordance to the protocol and with principles enunciated in the current version of the Declaration of Helsinki and the guidelines of Good Clinical Practices (GCP) issued by ICH. The CEC will receive annual safety report and interim reports and be informed about study stop/end in agreements with local requirements.

### 2.6 Declaration of interest

The principal investigator and the co-investigators declare that they have no conflict of interest.

### 2.7 Patient Information and Informed Consent

Informed consent process will be conducted prior to inclusion by trained and delegated research clinicians. Research clinicians will explain to each participant (meeting the inclusion criteria) the nature of the study and its aims, the procedures involved, the expected duration, the potential risks and benefits it may entail, and the financial compensation (gift certificates of increased value for

each follow-up assessment completed, i.e. 20, 30, 40, and 50 CHF for the 1-, 3-, 6-, and 12-month follow-up, respectively). Each participant will be informed that study participation is voluntary and he/she may withdraw from the study at any time and that study withdrawal will not affect his/her subsequent medical treatment.

As allowed by Article 18 of the Swiss Federal Act on Research involving Human Beings (Human Research Act, HRA), the information sheet will provide incomplete information regarding the randomization to different interventions. The information sheet will not mention the two distinct intervention groups to avoid a source of bias due to potentially different behavior depending of the intervention that participants will be randomized to. As required by Art. 18 HRA, this information will be provided, but at the end of the follow-up. At that time, the participant will have the possibility to consent to the use of the collected data or to refuse this use. In agreement with Art. 18 HRA, paragraph 3, data will be used only if the participant consents to it. All participants will receive a participant information sheet and a consent form (see Appendices) describing the study and providing sufficient information for participant to make an informed consent decision about their participation in the study. Research clinicians will be required to take time to ensure that all participants understand the nature of the study, its purposes, duration and the potential risks and benefits it entails. The latter points will therefore been carefully explained by trained research assistants. After providing all information, research clinicians will administrate the University of California, San Diego Brief Assessment of Capacity to Consent (UBACC; Jeste, 2007) to ensure that all participants understand study information. The UBACC was developed as a practical instrument to assess decision-making capacity. It has been successfully used to screen for capacity to consent within a research among frequent ER users with severe alcohol use disorders, which are often excluded from research, in part because assessing capacity to provide consent is challenging (McCormack et al., 2014). Participants will then been given time to read carefully the participation information sheet (which will cover the points discussed with the research clinicians) and the consent form. Enough time will given to the participants to decide if he/she wants to participate in the study. The research clinicians will answer all questions and provide participants with additional information when necessary.

The participants will be ask if they consent to participate in the questionnaires (baseline and follow-up) and the intervention which are the essential parts of the study. Additional (optional consent) will be asked for the audio-recording of the intervention and consultation of their hospital administrative and medical records. Participants refusing these optional consents will not be excluded from the study.

The participant will date and sign the informed consent form. Then the form will be dated and signed by the research clinician. A copy of the fully signed informed consent will be given to the participant together with the information sheet. The originally signed informed consent will be retained as part of the study records.

An additional consent procedure will be conducted at the end of the baseline procedures. Participants will be asked for consent to take a 2-3 centimeters long strand of hair (diameter of pencil lead) for testing of Ethyl glucuronide (EtG) at baseline, 6-, and 12-month follow-up. EtG in head hair has been presented as the only biomarker that can conclusively discriminate active heavy drinkers from social and non-drinkers (Crunelle et al., 2014). EtG concentration will be a secondary, confirmatory outcome measure. Participants with head hair shorter than 2 centimeters or refusing hair sampling will not be excluded from the study. An additional consent procedure at the end of the baseline procedure since the sampling might be felt as more invasive than questionnaires and brief intervention and might lower participant willingness to participate to the essential parts of the study.

During the pre-testing phase (Aim 1), information and consent procedure will also be used (see Appendices). The participants will be ask if they consent to participate in an audio-recorded brief motivational intervention and a semi-structured qualitative interview. There will be no questionnaires and no follow-up.

For mechanisms analyses (Aim 3), 15-20 minute qualitative semi-structured interview are planned after follow-up questionnaire for a randomly selected sub-group (N=10 participants in BMI group and N=10 in BA group at 1-month follow-up; and N=10 participants in BMI group and N=10 in BA group at 12-month). This interview will happen right after follow-up questionnaire interview. At that moment, the interviewer will provide information on the type of questions, their goal, and the resulting increase in questionnaire length. As for any other follow-up questions, participants will be allowed not to answer these questions.

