### 5.2 Secondary Outcomes

Secondary outcomes measures will be

a) Weekly drinking amount (i.e. number of drinks per week, derived from the TLFB).

b) Frequency of alcohol-related consequences (derived from 9 alcohol-related consequences adapted from Wechsler *et al.*, 1994). Consequences will be measured over the same 3 follow-up times (3-, 6-, and 12-month after intervention). Consequences are another validated way of measuring alcohol-related problems.

c) SIP sub-dimension scores (Physical, Social, Intra-personal, Inter-personal, and Impulse control; Kiluk *et al.*, 2013). These scores will be measured over the same 3 follow-up times (3-, 6-, and 12-month after intervention). Sub-dimensions of the SIP instrument have been proposed as additional variables of interest. Intervention might have an effect on different sub-dimensions but not other.

d) Proportion of patients with hazardous or harmful drinking status (Alcohol use disorder identification test - AUDIT score  $\geq 8$ ; Babor *et al.*, 2001) at 12-month follow-up. The AUDIT was developed by the WHO and is largely used to evaluate the effect of brief alcohol intervention. The reference period is 12 months and will thus be assessed only at this follow-up.

e) Proportion of patients who started alcohol treatment and of patients readmitted to the ER over the 12-month follow-up period. These will be measured at 3 follow-up times (3-, 6-, and 12-month after intervention). Effective referral to alcohol treatment and/or avoidance of alcohol-related ER readmission is a secondary objective of the tested intervention.

f) Proportion of patients who started alcohol treatment and of patients readmitted to the ER according to Lausanne University Hospital medical records. Participants will be asked for an additional, non-mandatory consent to have access to their administrative records at Lausanne University Hospital. This measure will be used as a confirmatory measure of patient self-report. It will also allow for evaluating participants lost to follow-up.

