## **8.5 Data Collection and Follow-up for withdrawn participants**

Investigators will not withdraw participants from the study. Participants may withdraw from the study at any time and might be lost to follow-up.

Participants withdrawing from the trial will not be contacted for subsequent questionnaires. However, if they consented to within the initial consent process, their hospital administrative records will be consulted to have an objective, non self-report measure of readmission in the ER and alcohol treatment at 12 months post baseline.

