### **11.2 Determination of Sample Size**

Based on studies with similar population (intoxicated young adults), setting (ER), and intervention (MI or BMI), we anticipate small to medium effects in favour of participants in the BMI group on alcohol use measures and alcohol-related problems (Monti et al. 1999; Smith et al. 2003; Spirito et al. 2004; Sommers et al. 2006; Monti et al. 2007).

Using a program for power analysis in longitudinal design (Rochon, 1998) a sample of N=172 patients per group (with attrition of 5-20% over follow-ups) will be required to detect small/medium effect sizes (.25), with power at .8, alpha at .05, and moderate autocorrelation dampening in GEE models for the primary outcomes.

The total sample size will thus be of 344 participants (1:1 ratio).

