### **11.4 Planned Analyses**

#### **11.4.1 Datasets to be analysed, analysis populations**

Primary analyses of the efficacy of the intervention (randomized controlled trial) will use all data available from all participants included in the trial. Analysis will be performed in an intention to treat paradigm (i.e. participants having left the ER without finishing the intervention, and/or not receiving intervention booster sessions will be analyzed in the intervention group).

Secondary analysis of mechanisms (Aim 3 of the project) will use data available for the corresponding analyses (e.g. participants with audio-recorded sessions for psycholinguistic coding; randomly selected sub-sample for qualitative analyses). Also, moderation analyses are designed as part of the mechanism analyses. For these, the relative efficacy of the BMI will be tested as an interaction with participants' characteristics, such as age, gender, alcohol problems severity, readiness to change, or personality traits.

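### The end-of-follow-up consent to data use has no route for participants lost or withdrawn earlier, and read literally it conflicts with the intention-to-treat analysis of all available data

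*Protocol*

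**What the plan says.** Protocol section 2.7 explains that the information sheet will not mention the two intervention groups. On when participants learn of them it says: "As required by Art. 18 HRA, this information will be provided, but at the end of the follow-up". It continues: "At that time, the participant will have the possibility to consent to the use of the collected data or to refuse this use". The rule that closes this account has no exception: "In agreement with Art. 18 HRA, paragraph 3, data will be used only if the participant consents to it".

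Other sections speak as if data stay usable without this second consent:

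- 11.4.1 says that the primary analyses "will use all data available from all participants included in the trial", by intention to treat. Sections 6.1.2.2 and 11.5 say the same. Section 7.4 counts a participant as included from the first signature.
- 8.5 says: "Participants withdrawing from the trial will not be contacted for subsequent questionnaires". It then has their hospital records consulted if they agreed to that in the initial consent. Section 9.2.5 repeats this.
- 5.2 f says of the hospital records: "It will also allow for evaluating participants lost to follow-up".
- 11.2 sizes the trial at 172 per group "with attrition of 5-20% over follow-ups".

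The month-12 procedures (9.3.6 to 9.3.8) list no disclosure or data-release step, and the table in 9.1 marks information and consent at baseline only.

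**The concern.** The second consent comes about a year after randomisation, and nothing says how it is sought from someone who can no longer be reached or who has withdrawn. If such people are not asked, the rule in 2.7 bars everything already collected from them: baseline, month 3, month 6 and hospital records.

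Three things are at stake.

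- The analysis set would be decided by events after randomisation: being reached at month 12 and agreeing once told of the two groups. A larger sample does not cure that kind of selection.
- The repeated-measures analysis would lose whole people, not only their later visits. Imputation under 11.5 could not rescue them, because data that may not be used cannot feed an imputation model. The baseline AUDIT score for which 11.4.2 adjusts every model would also be lost.
- The hospital records meant to show what happened to lost participants would be closed for those same participants.

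An analysis plan cannot settle this, because it cannot override a condition of consent.

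**Working it through.** **1. The sections side by side**

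| Participant | Under 2.7, read literally | Under the other sections |
|---|---|---|
| Lost after month 3 or month 6 | No second consent, so no data used | Earlier visits analysed (6.1.2.2, 11.4.1, 11.5); records used to evaluate the person (5.2 f) |
| Withdrawn | No further questionnaires, and no contact for release described | Earlier data analysed; records consulted on the initial consent (8.5, 9.2.5) |
| Completes, then refuses | No data used | Counted among all included participants (7.4, 11.4.1) |

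The two columns cannot both be followed unless a second consent is obtained by some route that the protocol does not describe.

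**2. The plan's own sample size**

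Inputs from 11.2: effect 0.25, power 0.8, alpha 0.05, attrition 5-20%, 172 per group. Section 5.1 gives three follow-ups. Assumptions, because the protocol gives no values: a two-sided test; retention of 95%, 87.5% and 80% at months 3, 6 and 12; a constant effect; correlation ρ^(lag^θ) with visits numbered 1, 2, 3.

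Formula: n per group = 2(1.960 + 0.842)² / (0.25² × I), where I is the information per randomised participant.

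With ρ = 0.5 and θ = 0.5, the correlation is 0.5 at lag 1 and 0.5^1.414 = 0.375 at lag 2. One visit then carries information 1, two visits 2/1.5 = 1.333, and three visits 1.571.

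- I = 0.075 × 1 + 0.075 × 1.333 + 0.80 × 1.571 = 1.432
- n = 15.70 / (0.0625 × 1.432) = 176 per group

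With ρ = 0.5, θ = 1 gives 167 and θ = 0 gives 183. The stated 172 is therefore compatible with a correlation near 0.5. It cannot be confirmed, because no correlation is given. The calculation keeps visits made before dropout.

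**3. People affected in the worst case**

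- 5% loss: 344 × 0.05 = 17.2, about 17 people, leaving about 327.
- 20% loss: 344 × 0.20 = 68.8, about 69 people, leaving about 275, or 172 × 0.80 = 137.6 per group.
- With the assumed retention, month-3 data collected but unusable: 344 × (0.95 − 0.80) = 51.6, about 52 people.
- Month-6 data likewise: 344 × (0.875 − 0.80) = 25.8, about 26 people.

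**4. Power at 20% loss**

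Power = Φ(0.25 × √(172 × I / 2) − 1.960).

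- All available data: I = 1.432, so Φ(2.774 − 1.960) = 0.79.
- Those reached at month 12 only: I = 0.80 × 1.571 = 1.257, so Φ(2.599 − 1.960) = 0.74.
- Number per group that would restore 0.80: 15.70 / (0.0625 × 1.257) = 200.

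Over ρ from 0.4 to 0.7 and θ from 0 to 1, power runs from 0.71 to 0.85 with all available data and from 0.64 to 0.81 with completers only. The drop is 4 to 7 percentage points throughout (0.849 to 0.807 at one end, 0.706 to 0.640 at the other). Refusals would come on top, but the protocol gives no rate.

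**The case against.** A reader might infer that lost and withdrawn participants are never asked, so that they vanish from the analysis and intention to treat becomes impossible. The protocol does not say so. Section 2.7 fixes a time for the request and does not tie it to completing the month-12 interview. Sections 8.5 and 9.2.5 rule out contact for questionnaires, not for disclosure and consent. Name, address and phone are collected at baseline (9.3.1 D), and identifiers are kept for 10 years after study completion (2.8). A letter or call is possible under the present text. The consent forms, which may describe the step, are appendices that are not at hand. This part of the objection stands: complete loss is a worst case.

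A reader might also infer a definite bias, or refusal that differs by group. Neither can be sized. Section 2.7 says that the groups are disclosed, not that participants learn their own group, and no refusal rate or dropout pattern is given.

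It can also be argued that data that may not be used are not available data, so 11.4.1 is not contradicted, and that consulting records is collection rather than use. This is less persuasive. Section 11.4.1 refers to all included participants, 7.4 defines inclusion by the first signature, and 5.2 f plainly intends the records of lost participants to be used. If the authors meant those data to stay usable, 2.7 is drafted too strictly and still has to be changed.

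**Conclusion.** The point holds as a conflict between sections and a missing route, not as proof that the planned analysis cannot be carried out. Followed as written, the rule in 2.7 is incompatible with 6.1.2.2, 11.4.1 and 11.5 and with the use of records in 5.2 f, 8.5 and 9.2.5, and it lets events after randomisation choose who is analysed for both primary outcomes.

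The worst-case size assumes that nobody lost or withdrawn is recovered. It rests on the stated 5-20% attrition and on assumed retention and correlation values. The loss of power is moderate. Selection is the more serious risk, but its direction and size are hypothetical on the figures in the protocol.

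**What to change.** - **2.7:** state that disclosure and the request for data release take place after the month-12 outcome interview, at withdrawal, and by letter or phone to every randomised participant not reached at month 12. Staff who do not conduct the blinded interviews should handle this.
- **Ethics committee:** agree how the data of those who do not reply are treated, and write the answer into 2.7.
- **5.2 f, 8.5, 9.2.5 and 11.4.1:** reconcile with 2.7, so that the analysis set and the use of hospital records follow from one rule.
- **Reporting:** give the number of participants whose data were not released, by group.
- **11.2:** restate power with attrition as loss of whole people only if the data of non-responders cannot be used.

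The cost is a protocol amendment, an ethics query and a mailing; no extra participants are needed. The drawback is that some further withdrawn participants may refuse once they are asked.

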## **2.8 Participant privacy and confidentiality**

A special attention will be given to maintain the confidentiality of data provided by the participants. Direct subject identifiers (e.g., participants' names, contact information) will be collected to facilitate follow-up communication and thereby conduct the whole study. To ensure confidentiality of data, all data collected on participants in the eCRF—including lab tests (i.e., head hair samples)—will be identified with a randomly generated, unique participant identification number (PIN). Master lists of PINs and individually identifiable private information will be stored in locked file cabinets and password-protected computers with restricted access. These lists will be available only to research staff on this project. The linkage and the direct subject identifiers will be destroyed 10 years after study completion.

For data verification purposes, authorized representatives of the Sponsor (the Clinical Trial Unit-Lausanne) or a CEC may require direct access to parts of the medical records relevant to the study, including participants' medical records.

Information regarding privacy and confidentiality will stand in the information sheet. It will also be specified that the principal investigator will permit trial-related monitoring, audits or CEC reviews, which may entail provision of direct access to participants' identifiers.

